Interventions^b^	Each individual would be assigned to 1 of the 4 following strategies: Control group (habitual diet, ie, typical North American diet) Adherence to Canada’s Food Guide recommendations on healthy food choices Adherence to Canada’s Food Guide recommendations on healthy food choices and including a high-protein reformulation Adherence to Canada’s Food Guide recommendations on healthy food choices, including a high-protein reformulation and a minimal physical activity component Each strategy is followed until the end of follow-up. Participants assigned to a lifestyle strategy are expected to maintain their dietary intake or amount of physical activity at or above the prespecified threshold by the corresponding intervention strategy.	The intervention component will be the same as that specified in the target trial. Furthermore, we will assume that each dietary assessment period (ie, within 2 months beginning at each time point) accurately reflects the average diet in the interval between follow-ups.
Assignment	Participants are randomly assigned to a dietary strategy but are not blinded to their assignment.	We will attempt to emulate randomized assignment by adjusting for dietary intakes before baseline and baseline covariates.
Outcomes	The outcomes are physical function and muscle strength, general health indicators, and cognitive health.	The outcomes will be physical function and muscle strength, general health indicators, and cognitive health.
Time zero and follow-up	The study starts at baseline and ends at incomplete follow-up or 3 years after baseline, whichever occurs first.	The study will start at baseline and end at incomplete follow-up or 3 years after baseline, whichever occurs first. An incomplete follow-up is defined as missing data for questionnaires (nonresponse or loss to follow-up) or missing outcome data at the end of follow-up.
Causal contrast^c^	Intention-to-treat effect Per-protocol effect	Observational analog of both contrasts: Secondary: intention-to-treat effect Primary: per-protocol effect

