Statistical analysis	Intention-to-treat analysis: apply inverse probability weighting with adjustment for prebaseline and baseline factors associated with incomplete follow-up to account for study dropouts Per-protocol analysis: apply the parametric g-formula algorithm to compare postintervention outcomes between groups receiving each treatment strategy, adjusting for pre- and postbaseline factors associated with adherence to intervention strategies and incomplete follow-up.	Analysis will be the same as that specified in the target trial for both contrasts. However, the observational analog will require additional adjustments for confounding at baseline and before baseline due to previous dietary pattern.

^a^FFQ: food-frequency questionnaire.

^b^Refer to the *Hypothetical Interventions* section for detailed intervention.

^c^The observational analog of the intention-to-treat contrast corresponds to the baseline values of the intervention, which are assigned and initiated at the same time.

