### Time Zero and Follow-Up

In the target trial of a sustained lifestyle intervention, participants would be met at baseline and then regularly to ensure that diet and physical activity habits are consistent with the intervention assigned by the random allocation. The hypothetical diet and physical activity intervention would be assigned and initiated at baseline. In the emulation, annual follow-ups with comprehensive diet, physical activity, and covariate data collection are available to emulate the hypothetical intervention. Hence, participants would be followed from the study baseline (time point 0; ie, the time at which the intervention strategy would also be assigned and would begin), at each year (ie, time points 1 and 2), and until the end of the study (time point 3). We also assume that the diet and physical activity habits measured at each follow-up time adequately reflect the habits during the entire year.

The end of follow-up outcome measurements will be used to estimate the effect of the sustained lifestyle intervention strategy. Measures of dietary intake and physical activity throughout the study (ie, time point 0 to time point 3) will be used to emulate the sustained lifestyle intervention. Dietary intakes in the year preceding the intervention will be estimated using the frequency questionnaire completed at baseline (ie, time point 0). Missing covariate data at a given follow-up will be carried forward once, after which participants will be considered as having incomplete follow-up.

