Figure 2 presents the causal directed acyclic graph (DAG) of the hypothesized relationship between a sustained lifestyle intervention strategy (*X_0_, X_1_*) and an end of follow-up outcome *Y* for 1 follow-up after baseline (year 1). The model is limited to year 1 for clarity, but the hypothesized causal structure extends to additional follow-ups. The exposure of interest *X_k_* is the joint and cumulative effect of a sustained diet and physical activity intervention strategy measured at baseline and follow-ups.

In the context of this target trial emulation (Figure 2), *P* includes dietary habits before the baseline assessment. *P* can have an effect on baseline dietary habits (eg, previous healthy habits increase the likelihood of baseline healthy habits) and dietary habits throughout the target trial emulation (eg, previous healthy habits increase the likelihood of adhering to healthy habits). Furthermore, *P* influences baseline and time-varying confounding. Finally, given the long-term effect of chronic exposure, *P* potentially affects *Y* directly.

The intention-to-treat analysis is similar to the per-protocol analysis. However, only baseline diet and physical activity habits and covariates are considered, as well as prebaseline diet and physical activity. In both the per-protocol and intention-to-treat analyses, loss to follow-up (eg, nonresponse or missing follow-up and health outcomes not measured) will be accounted for using g-methods such as inverse probability weighting.

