#### Dietary Assessment

In NuAge, diet during the year before baseline was assessed using 1 semiquantitative food-frequency questionnaire [47]. Dietary intakes at baseline (ie, time point 0) and each annual follow-up (ie, time points 1, 2, and 3) were assessed using 3 repeated face-to-face interviewer-administered 24-hour dietary recalls.

Dietary intakes measured using 24-hour dietary recall are more accurate (ie, have less systematic error or bias) than food-frequency questionnaire [48-50] but are particularly affected by random measurement error (ie, within-individual random error) [50]. When several variables measured with errors are considered simultaneously in a regression model, the regression coefficients may be biased in any direction [51]. To account for random measurement error, the National Cancer Institute Markov Chain Monte Carlo (NCI MCMC) multivariate method could be applied [52]. However, the combination of the parametric g-formula and multivariate measurement error correction using the NCI MCMC method is not feasible. The NCI MCMC method estimates time-invariant measurement error–corrected intakes, while the g-formula algorithm is designed for time-varying exposures.

Recognizing the importance of accounting for measurement error, the correction for measurement error will be reserved for the secondary intention-to-treat analysis. For the intention-to-treat contrast, the time-varying values of exposure and the time-varying values of confounding are not considered. Thus, the NCI MCMC method will be used to obtain measurement error–corrected estimates of the relationship between dietary intakes measured at baseline and outcome at the end of follow-up. Notably, the three 24-hour dietary recalls collected at each time point contribute to reducing random errors, at least to some extent, even in the absence of measurement error correction.

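### The intention-to-treat analog shares a definition of incomplete follow-up that includes missing questionnaires, so as written it can censor participants whose year-3 outcome was measured

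*Protocol article*

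**What the plan says.** In Table 1 (section Target Trial), the emulation column for time zero and follow-up reads: "The study will start at baseline and end at incomplete follow-up or 3 years after baseline, whichever occurs first". It then defines the terminating event: "An incomplete follow-up is defined as missing data for questionnaires (nonresponse or loss to follow-up) or missing outcome data at the end of follow-up". The next row names two contrasts, "Secondary: intention-to-treat effect Primary: per-protocol effect", and nothing in the table gives them separate rules. For the intention-to-treat analysis, the statistical row says to "apply inverse probability weighting with adjustment for prebaseline and baseline factors associated with incomplete follow-up to account for study dropouts". The emulation takes over that analysis and adds adjustment for baseline and prebaseline confounding.

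The section Modeling of Hypothetical interventions says of the intention-to-treat analysis: "However, only baseline diet and physical activity habits and covariates are considered, as well as prebaseline diet and physical activity". It adds that in both analyses "loss to follow-up (eg, nonresponse or missing follow-up and health outcomes not measured) will be accounted for using g-methods such as inverse probability weighting". The section Dietary Assessment confirms: "For the intention-to-treat contrast, the time-varying values of exposure and the time-varying values of confounding are not considered".

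Two provisions limit the censoring. Time Zero and Follow-Up states: "Missing covariate data at a given follow-up will be carried forward once, after which participants will be considered as having incomplete follow-up". Causal Contrast, in its discussion of the per-protocol analysis, does not count participants with major post-baseline events as incomplete, provided that they attended the annual assessment and that such events are numerous enough.

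**The concern.** The per-protocol g-formula models exposure and covariates at every time point, so ending follow-up when those data run out has a reason there. The intention-to-treat analog has no such need, because a participant with complete baseline data and a measured year-3 outcome supplies everything it uses. Under the shared definition, such a participant can still be treated as censored.

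Two things are at stake. First, observed outcomes are given up and the estimate leans on a weight model where it need not. Second, the weights rest on prebaseline and baseline factors. In this age group, interim nonresponse plausibly follows illness or declining function after baseline. The protocol itself lists lengthy hospitalization, prolonged bed rest and incident cancer as events that limit participation. If such events cause missed questionnaires and also affect year-3 function, baseline-only weights cannot remove the resulting selection, whereas keeping the observed outcome avoids it.

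The analog also has a second use. The section Sensitivity Analysis to Assess the Impact of Measurement Error extrapolates from its corrected and uncorrected estimates to the primary per-protocol result.

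**Working it through.** **Reading the text**

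1. Scope: the end-of-follow-up rule and its definition appear once in Table 1 and cover both contrasts.
2. Data needed by the analog: prebaseline and baseline values (Modeling of Hypothetical interventions; Dietary Assessment) and the year-3 outcome. No post-baseline exposure or covariate enters.
3. Exemption: no section frees the analog from the questionnaire criterion or says that a later measured outcome is kept.
4. Carry-forward: it is worded for covariate data. The Assignment section labels diet and physical activity as treatment (X), separate from the time-varying covariates (L). Activity is a covariate only in the diet-only models. Whether a missed set of recalls or activity items is carried forward is therefore not settled.

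**Size, for illustration only**

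The protocol gives no nonresponse or dropout figure, so there is no stated result to reproduce. The cohort size, 1753, is the only input from the document. These inputs are assumed:
- The year-3 outcome is available for 90%: 1753 × 0.90 = 1577.7, about 1578.
- Nonresponse is q at each of years 1 and 2, with q = 2%, 5%, 10% or 15%, unrelated to whether the year-3 outcome is measured.

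Share of measured outcomes censored under three readings:
- A, carry-forward applies and misses are independent (both visits must be missed): q².
- B, carry-forward applies and half of those who miss year 1 also miss year 2: 0.5q.
- C, any missed diet or activity questionnaire ends follow-up: 1 − (1 − q)².

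| q | A | B | C |
|---|---|---|---|
| 2% | 0.04%, 1 | 1.0%, 16 | 4.0%, 62 |
| 5% | 0.25%, 4 | 2.5%, 39 | 9.8%, 154 |
| 10% | 1.0%, 16 | 5.0%, 79 | 19.0%, 300 |
| 15% | 2.3%, 35 | 7.5%, 118 | 27.8%, 438 |

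Losing a share f multiplies the standard error by 1/√(1 − f), before any variance from the weights. At q = 15% this is 1/√(1 − 0.0225) = 1.011 for A, 1/√(1 − 0.075) = 1.040 for B and 1/√(1 − 0.2775) = 1.176 for C.

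If 80% have the outcome (about 1402), the ranges become 1 to 32 (A), 14 to 105 (B) and 56 to 389 (C). A missed year-3 questionnaire with a measured year-3 outcome is not counted here and would raise the figures.

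**The case against.** The strongest reply is that the protocol nowhere says measured year-3 outcomes are discarded in this analog. Its weights are meant for dropouts, and someone examined at year 3 is not naturally a dropout. The wording on loss to follow-up in Modeling of Hypothetical interventions does not name interim questionnaires and can be read narrowly. An article may also leave the coding of analysis sets to a fuller plan. This stands in part: the loss of outcomes is inferred from the rule. But the definition is printed, covers both contrasts and carries no exemption, so an analyst who follows it would censor these people.

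A reader might infer that one missed interim questionnaire always ends follow-up. The document does not support that for covariate data, which are carried forward once. For diet and activity data the text is unclear, which is why the range above is so wide.

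A reader might also apply a flat 3% to 15% loss to the whole cohort: 1753 × 0.03 = 53 and 1753 × 0.15 = 263. Those rates are assumed, ignore carry-forward, and use the cohort before the baseline-completeness exclusions. They should not be read as an estimate.

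The excused-participant exception also limits censoring for illness, but it requires attendance and so does not help someone who missed the assessment.

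Finally, a sample aligned with the per-protocol one can be defended for the measurement-error comparison, because its purpose is to extrapolate to that analysis. This is a fair point, and the fix allows for it.

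**Conclusion.** The point holds in a limited form. A definition suited to the per-protocol contrast also governs the intention-to-treat analog. As written, it can censor participants with a measured year-3 outcome for lacking data the analog does not use, and baseline-only weights cannot fully repair selection that arises after baseline.

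The size cannot be derived from the document. On the assumed rates it runs from about 1 outcome to about 438 of 1578. Whether carry-forward covers diet and activity data, and how far misses persist between visits, have a large effect on where it falls. Under carry-forward with independent misses the loss of precision is negligible, at most about 1.1% in standard error.

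The reach is also limited. This concerns the secondary contrast and, through the sensitivity analysis, the extrapolation about measurement error. A reader might infer that the primary result is biased by the rule. The document does not support that, because the per-protocol analysis does use interim data. A cheap correction is warranted; this is not a failure of the main analysis.

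**What to change.** - In Table 1, define incomplete follow-up by contrast. For the intention-to-treat analog it should mean only a missing year-3 outcome, judged outcome by outcome. Participants with missing interim questionnaires stay in with their observed value.
- Keep questionnaire-based censoring for the per-protocol contrast. Reconcile Table 1 with Time Zero and Follow-Up, stating whether the single carry-forward also covers dietary recalls and physical activity.
- Report both analysis sets, with the number of participants who have a year-3 outcome but incomplete interim questionnaires.
- Run the corrected-versus-uncorrected measurement-error comparison on one common, stated sample, so that any difference reflects the correction and not the participants.

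The cost is a sentence or two in Table 1, a clarification of the carry-forward rule and one change to the analysis-set code. No new data are needed. The two contrasts will then rest on different analysis sets, which should be explained when they are compared.

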### Study Design and Sample

Data from the NuAge prospective cohort will be used to emulate the target trial [25]. The NuAge cohort comprised 1753 generally healthy community-dwelling adults aged 67 to 84 years at baseline and followed for 3 years. The baseline and each annual follow-up evaluation included a comprehensive assessment of sociodemographic data, diet, physical activity, functional status, as well as physical and mental health status [25].

The NuAge sample is relevant to our research question. The target population of CFG recommendations comprises all individuals aged ≥2 years, which is compatible with the NuAge target sample of generally healthy older adults from the greater Montreal, Sherbrooke, and Laval areas of the province of Quebec, Canada.

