### Assignment

We will attempt to emulate random allocation or randomization by adjusting for dietary intakes in the year before the intervention, as well as adjusting for covariates at the start of the study. Covariates were identified using the causal diagrams depicted in Figure 1, based on background knowledge of the relationship between the hypothetical lifestyle intervention and outcomes.

Dietary components that are the foundation for healthy eating in CFG include intakes of vegetables and fruits, whole grains, protein foods (plant- and animal-based protein foods, milk, and plant-based beverages with protein), and unsaturated oils and fats [1].

Covariates, including age at baseline, biological sex, region, education, living alone, smoking and drinking (alcohol) habits, major chronic diseases (ie, hypertension, diabetes, cancer, and heart disease), the number of medications, supplement use (eg, vitamins and minerals), and height and weight, are as follows:

*Z*, baseline covariates: age, sex, region, education, history of smoking, height, and former cancer history*P*, previous exposure (ie, exposure of time-varying intervention before baseline): dietary habits before baseline*L*, (time-varying) covariates: weight, number of medications, supplement use, living alone, major chronic diseases (eg, hypertension, diabetes, cancer, and heart disease), and smoking and alcohol habits*X*, (time-varying) treatment: diet and physical activity habits*Y*, end of follow-up outcome: muscle health, general health, and cognitive health

Contrary to dietary habits, data on physical activity habits before baseline were not collected in NuAge. In this case, the potential effect of previous physical activity habits will not be accounted for in the models that aim to emulate the sustained physical activity intervention strategy. For the models emulating the sustained diet intervention strategy only, physical activity habits during the study will be used as a covariate, hence mitigating the confounding of previous physical activity, at least to some extent.

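### Baseline-only dropout weights can leave selection bias in the secondary intention-to-treat analog if baseline diet affects later illness or illness-related dropout

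*Protocol article*

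**What the plan says.** The statistical analysis row of Table 1 sets the dropout handling for the intention-to-treat contrast: "apply inverse probability weighting with adjustment for prebaseline and baseline factors associated with incomplete follow-up to account for study dropouts". The emulation column carries this over ("Analysis will be the same as that specified in the target trial for both contrasts") and adds only further adjustment for confounding at and before baseline.

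The text agrees. Under Modeling of Hypothetical interventions, the intention-to-treat analysis is one in which "only baseline diet and physical activity habits and covariates are considered, as well as prebaseline diet and physical activity". Under Dietary Assessment, for this contrast "the time-varying values of exposure and the time-varying values of confounding are not considered". The first of these sections also says that loss to follow-up in both contrasts will be handled by g-methods such as inverse probability weighting. That names a method and adds no postbaseline covariate to the intention-to-treat weights.

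For the per-protocol contrast, the same table row specifies "adjusting for pre- and postbaseline factors associated with adherence to intervention strategies and incomplete follow-up".

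The yearly data exist. Study Design and Sample states: "The baseline and each annual follow-up evaluation included a comprehensive assessment of sociodemographic data, diet, physical activity, functional status". The Assignment section classes weight, number of medications, supplement use, living alone, major chronic diseases, and smoking and alcohol habits as time-varying covariates L.

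**The concern.** Censoring weights built from baseline factors are valid only if, given those factors, dropout is unrelated to the outcome. The participants are 67 to 84 years old at entry and are followed for 3 years. New disease, weight loss or added medication can both lead someone to leave and lower the final strength or function score.

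The plan's own causal structure leaves room for this. The modeling section assumes feedback between the intervention and later covariates. The Causal Contrast section anticipates long hospitalization, bed rest and incident cancer after baseline. If diet at baseline changes the risk of such events, or how often they lead to dropout, completers are selected differently at different levels of diet, and baseline-only weights cannot undo that.

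At stake is the intention-to-treat analog itself. It is secondary, but it is the only analysis with measurement-error correction.

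**Working it through.** **No plan figure to reproduce.** The protocol gives N=1753 but no dropout rate, effect size or SD. Every rate and effect below is an assumption chosen to show the mechanism.

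**Closed form.** Assume illness during follow-up in 20% (habitual diet) and 12% (better diet), illness lowering the outcome by 0.8 SD, and dropout of 10% without illness and 50% with it. Read these rates as already conditional on the baseline factors in the weights. Otherwise the formula describes an unweighted completer analysis.

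Illness prevalence among completers = p(1 − d_ill) / [p(1 − d_ill) + (1 − p)(1 − d_well)]

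- Habitual diet: 0.20 × 0.50 / (0.10 + 0.80 × 0.90) = 0.10 / 0.82 = 0.122
- Better diet: 0.12 × 0.50 / (0.06 + 0.88 × 0.90) = 0.06 / 0.852 = 0.070
- True effect through illness: (0.20 − 0.12) × 0.8 = 0.064 SD
- Effect among completers: (0.1220 − 0.0704) × 0.8 = 0.041 SD
- Bias: 0.041 − 0.064 = −0.023 SD, or −36%
- With an added direct effect of 0.05 SD: 0.091 against 0.114, the same −0.023 SD, or −20%

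**Simulation.** Each scenario had 600,000 participants (Monte Carlo error about 0.003 to 0.005 SD). Baseline health affects baseline diet, illness, dropout and outcome. Diet has a direct effect of 0.1 SD and may also alter illness. Illness lowers the outcome by 0.6 SD unless stated and may alter dropout. Dropout weights from baseline health and diet were compared with weights that also used illness. Selected scenarios:

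| Diet lowers illness (log odds) | Dropout if ill / not ill | True | Baseline-only | With illness |
|---|---|---|---|---|
| 0 | 11.3% / 10.0% | 0.100 | 0.102 | 0.102 |
| 0 | 47.7% / 10.1% | 0.100 | 0.106 | 0.107 |
| 0.4 | 25.8% / 10.0% | 0.134 | 0.135 | 0.137 |
| 0.4 | 48.6% / 10.0% | 0.134 | 0.122 | 0.132 |
| 0.8 | 26.0% / 10.1% | 0.160 | 0.154 | 0.160 |
| 0.8 | 48.5% / 10.1% | 0.160 | 0.139 | 0.156 |
| 0.8 (illness costs 1.0 SD) | 48.5% / 9.9% | 0.200 | 0.167 | 0.197 |
| 0, but dropout (especially when ill) is less frequent with better diet | 17.7% / 8.3% | 0.100 | 0.082 | 0.098 |

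What the table shows:

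- When diet alters neither illness nor illness-related dropout, the two sets of weights agree and their departure from the truth is noise, even with 47.7% dropout among the ill.
- When diet alters illness and illness strongly drives dropout, baseline-only weights are off by 0.012/0.134 = 9%, 0.021/0.160 = 13% and 0.033/0.200 = 17%, all toward zero.
- When dropout itself depends on diet, they are off by 0.018/0.100 = 18%.
- With about 26% dropout among the ill, the bias is at most about 0.007 SD.

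The last column treats illness as known for everyone who left, so it is the best that the remedy could do.

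**Scale against precision.** If 84% of 1753 complete (1473) and two equal groups of about 736 are compared, the standard error of a mean difference is √(2/736) = 0.052 SD, or 0.036 SD with a residual SD of 0.7. The closed-form bias of 0.023 SD is roughly half a standard error.

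**The case against.** The strongest reply is that an intention-to-treat analog of a point intervention is meant to use baseline information only. That is right for the exposure and outcome model, where adjusting for postbaseline covariates would change what is estimated. It is no reason to leave them out of a model for dropout: used only in the censoring weights, they leave the estimand as it is.

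Four further objections stand, at least in part.

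- A reader might infer that illness-driven dropout by itself biases the contrast. It does not. Diet must also affect illness or illness-related dropout, and the documents say nothing about dropout rates or reasons.
- A reader might infer that the primary result is compromised. The primary per-protocol analysis already uses postbaseline factors for incomplete follow-up. The measurement-error sensitivity analysis compares corrected with uncorrected intakes inside the intention-to-treat analysis. Both versions share the dropout handling, so the bias should partly cancel in their difference. Nothing in the protocol lets one quantify what remains.
- A reader might take the different dropout handling of the two contrasts as an error in itself. They are different estimands, and the g-formula needs postbaseline covariates for adherence in any case. The table row shows only that the plan accepts postbaseline factors as predictors of incomplete follow-up.
- Covariates are updated once a year. Someone who falls ill between visits and never returns has no updated record, so the remedy cannot reach that illness.

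The provision that excuses participants with major events from the intervention does not answer the point, because it covers only those who still attended the annual assessment.

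**Conclusion.** The point holds in conditional form. The protocol states a covariate set for the intention-to-treat dropout weights that is poorer than the data allow, so this is a stated choice and not a detail left to a later plan. Given the feedback that the plan itself assumes, ignorable dropout given baseline factors alone is hard to defend.

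The illustrated bias of about 0.01 to 0.03 SD, roughly −9% to −36% of the effect, rests wholly on assumed inputs. The upper end needs a 40% relative reduction in illness from better diet, a fivefold rise in dropout with illness, and a diet effect that runs entirely through illness. In absolute terms the bias is small beside the likely sampling error. It is worth correcting because correction is cheap, not because the study's main conclusion depends on it.

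**What to change.** In the statistical analysis row of Table 1 and in the intention-to-treat paragraph under Modeling of Hypothetical interventions:

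- State that dropout weights are visit-specific and estimated from Z, P, baseline diet and activity, and the most recent time-varying covariates L_k.
- Re-estimate the weights in each of the bootstrap samples already planned (at least 200).
- Keep postbaseline covariates out of the exposure and outcome model, and make clear that the Dietary Assessment remark on time-varying values refers to that model and not to the dropout weights.
- Say whether the weights use corrected or uncorrected baseline intakes, since this contrast also uses the NCI MCMC correction.

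Stabilisation and truncation can be left to the analysis plan.

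No new data are needed. The costs are extra programming inside the bootstrap and somewhat more variable weights. Illness arising after the last attended visit remains uncaptured, so the report should describe the selection bias as reduced, not removed, and should give the number of dropouts by visit.
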